## Abstract

**Background:**

Patients experience considerable postoperative pain after spinal surgery. As the spine is located at the centre of the body and supports body weight, severe postoperative pain hinders upper body elevation and gait which can lead to various complications, including pulmonary deterioration and pressure sores. It is important to effectively control postoperative pain to prevent such complications. Gabapentinoids are widely used as preemptive multimodal analgesia, but their effects and side effects are dose-dependent. This study was designed to examine the efficacy and side effects of varying doses of postoperative pregabalin for the treatment of postoperative pain after spinal surgery.

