## Introduction

### Background and rationale

Postoperative pain after spinal surgery is debilitating for the patients due to its severe intensity. As the spine is located at the centre of the body to support body weight, severe postoperative pain hinders upper body elevation and gait, which can lead to various complications, including pulmonary deterioration and pressure sores [1, 2]. Effective control of postoperative pain is important for the prevention of such complications and for fast rehabilitation [3, 4].

Preemptive multimodal analgesia is often performed using acetaminophen and nonsteroidal anti-inflammatory drugs (NSAID) [5, 6]. However, NSAIDs have a risk of complications, such as renal toxicity, bleeding tendency, and cardiac events, limiting their use in the elderly or in patients with pre-existing renal insufficiency [7, 8]. NSAID use following spinal fusion has also been reported to increase the rate of nonunion [9]. In contrast, gabapentinoids including gabapentin and pregabalin are relatively safe for patients with renal or cardiac risk factors, do not hinder fusion after spinal surgery, show opioid-sparing effects, and decrease the adverse effects of intravenous patient-controlled analgesia (IV PCA) [10, 11]. Due to these advantages and their efficacy, gabapentinoids are widely used for the management of postoperative pain after various surgeries [12–14].

Pregabalin binds to the α2-δ protein subunit of presynaptic voltage-gated calcium channels in both the central and peripheral nervous systems, and it has a superior pharmacodynamic and pharmacokinetic profile to that of gabapentin [15]. It is a more potent and more effective analogue of gabapentin [16]. However, gabapentinoids are associated with several adverse effects, including sedation, dizziness, and peripheral oedema, which are known to be dose-dependent [17]. There is currently some controversy regarding the optimal safe dose of gabapentinoids.

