### Trial design

This will be a single-centre, randomized, prospective, double-blind, superiority clinical trial with four arms. The trial will include three treatment arms where pregabalin will be administered at different doses (25, 50, 75 mg), and one control arm where placebo will be administered. The participants will be equally distributed among the four arms.

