### Sample size

The prior calculation of the sample size indicated that at least 28 subjects were required for each group. For calculation, the software G*Power 3.1.9.7 was used with a statistical power of 0.95 at an effect size of 0.448 with an alpha level of 0.0167. The effect size was determined based on a previous study [18]. In this study, three groups—those treated with placebo, pregabalin 75 mg, and pregabalin 150 mg—each comprised 28 participants. The groups were compared based on their PCA usage, with mean values of 95.3, 96.6, and 105.2 respectively, and an approximate standard deviation of 10. For the purposes of this study, which involves four instead of three groups, a fourth hypothetical group was considered with the mean value of 96.6, which is the median value of the three established groups. Based on this data, Cohen’s *f* was calculated, resulting in an effect size of 0.448. To compare the four groups through Bonferroni’s test, the alpha level was set at 0.05 divided by 4, which is 0.0167. When calculated based on these parameters, the total sample size needed is found to be 112, and the number of participants needed per group is 28. Considering a follow-up loss of approximately 15%, 33 participants per group would be required, resulting in a total of 132 participants needed for the study.

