## Assignment of interventions: allocation

### Sequence generation

All patients will be randomized to one of the following four groups at a 1:1:1:1 ratio one day prior to surgery: P0 (*n* = 33), P25 (*n* = 33), P50 (*n* = 33), and P75 (*n* = 33) groups. The assignment will be conducted by computer-generated random sequence with block randomization, stratified by sex and age (< 65 and ≥ 65 years). Based on the potential risk of age and gender having an impact on the pain relief and side effect outcomes after surgery, as suggested by previous literature, we performed stratification accordingly [19]. To maintain an equal allocation of participants to each of the four treatment groups, we will use a block size of 4 (one allocation for each treatment group within a block). The generated sequence will be masked from the primary investigators and will be recorded in the randomization list.

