## Statistical methods

### Statistical methods for primary and secondary outcomes

The primary objective of this study is to compare the effect of different doses of pregabalin to placebo on pain relief and the need for additional analgesics during the 72-h period following surgery, at various time points. Additionally, the study aims to assess the incidence of adverse events during this period. Primary outcomes include the VAS pain score, total dose of IV PCA administered, and frequency of rescue analgesic administered. We will use the Kolmogorov–Smirnov test (K-S test) to assess the normality of the primary outcome measure. If the normality assumption is met, we will perform an analysis of variance (ANOVA) analysis; otherwise, we will use the Kruskal–Wallis test for comparison. We will use the Bonferroni’s method for conducting subgroup analysis to account for multiple comparisons. Categorical variables, such as the incidence and frequency of nausea and vomiting caused by IV PCA or the incidence of side effects (sedation, dizziness, headache, visual disturbance, and swelling), will be compared between the groups using the chi-squared test. Statistical analyses will be performed using SPSS 20.0 (IBM, Armonk, NY, USA). In all analyses, *P* < 0.05 will be taken to indicate statistical significance.

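### Side effects described as dose-dependent are compared only with a chi-squared test that ignores dose order; adding a prespecified trend test beside it is a cheap gain

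*Protocol article*

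**What the plan says.** In its section on statistical methods for primary and secondary outcomes, the protocol states that the incidence of nausea and vomiting, "or the incidence of side effects (sedation, dizziness, headache, visual disturbance, and swelling), will be compared between the groups using the chi-squared test". The same section sets the threshold: "In all analyses, *P* < 0.05 will be taken to indicate statistical significance". The section on additional analyses says that none are planned. Bonferroni's method is named for multiple comparisons, but it makes no use of dose order.

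The protocol treats the side effects as related to dose. The abstract says of gabapentinoids that "their effects and side effects are dose-dependent". The rationale lists adverse effects "including sedation, dizziness, and peripheral oedema, which are known to be dose-dependent". The Objectives section makes the safety of varying doses part of the aim. The design has "three treatment arms where pregabalin will be administered at different doses (25, 50, 75 mg), and one control arm where placebo will be administered".

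Arm sizes are "P0 (*n* = 33), P25 (*n* = 33), P50 (*n* = 33), and P75 (*n* = 33) groups", and the sample-size section says that "at least 28 subjects were required for each group" before allowance for loss. No expected side-effect rate appears anywhere.

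**The concern.** Pearson's chi-squared on a four-by-two table gives the same P-value however the four arms are relabelled. It spreads its power over every possible pattern of differences, whereas the protocol's own background points to one pattern: incidence rising with dose. A test that scores the arms by dose puts its single degree of freedom on that pattern.

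What is at stake is how a non-significant result will be read. The Discussion already anticipates pain relief without major side effects at the lowest dose. If the overall chi-squared is the only inferential result for a side effect, a non-significant value may be taken as showing no relation between dose and that side effect, when the test had limited power to detect one.

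**Working it through.** **Inputs from the protocol.** Four arms at 0, 25, 50 and 75 mg; 33 per arm randomised; 28 per arm after the planned loss; significance at 0.05, taken as two-sided for the trend test.

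**The protocol's own figure.** The sample size is stated "with a statistical power of 0.95 at an effect size of 0.448 with an alpha level of 0.0167". A one-way ANOVA with four groups and noncentrality N × 0.448² gives N = 112, or 28 per group (power 0.955). Then 28/(1 − 0.15) = 32.9, rounded up to 33. Both arm sizes reproduce from the stated inputs. They concern analgesic use; no power is stated for side effects.

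**Assumption.** Side-effect rates per arm are not given, so several patterns are tried.

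**Tests compared.** Let x0, x1, x2, x3 be the numbers with the event in the four arms, n the arm size, T their sum and p = T/(4n).

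- Overall chi-squared: X² = Σ(xi − T/4)² / [n p(1 − p)], significant if it reaches the 5% point on 3 degrees of freedom (7.815).
- Exact Cochran-Armitage trend: S = x1 + 2·x2 + 3·x3. Given T, its null mean is 1.5T. The two-sided P-value is the conditional probability of a value of S at least as far from 1.5T as the one observed.

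Power is the sum of the binomial probabilities of all significant tables, by full enumeration: 29⁴ = 707,281 tables at n = 28 and 34⁴ = 1,336,336 at n = 33.

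| Assumed incidence at 0/25/50/75 mg | n per arm | Chi-squared | Exact trend |
|---|---|---|---|
| 5/10/15/25% | 28 | 0.42 | 0.57 |
| 5/10/15/25% | 33 | 0.51 | 0.66 |
| 5/10/15/20% | 28 | 0.26 | 0.38 |
| 5/10/15/20% | 33 | 0.32 | 0.46 |
| 2/5/10/20% | 28 | 0.47 | 0.65 |
| 2/5/10/20% | 33 | 0.57 | 0.73 |
| 5/5/5/20% (top dose only) | 33 | 0.53 | 0.50 |
| 5/20/20/20% (plateau) | 33 | 0.36 | 0.29 |
| 5/10/25/10% (umbrella) | 33 | 0.54 | 0.13 |

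For the steady gradients the gain is about 12 to 17 points. As a ratio it runs from 0.66/0.51 = 1.3 to 0.38/0.26 = 1.5. For the other three shapes the trend test gains nothing or loses.

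**Where the gain comes from.** It comes from dose order, not from exactness. At 5/10/15/20% and n = 33, an exact test that ignores order has power 0.31, against 0.32 for chi-squared.

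**Small counts.** The expected number of events per arm is T/4, which is below 5 when T is below 20. That is an overall incidence below 20/132 = 15.2% at 33 per arm, or 20/112 = 17.9% at 28. The true size of each nominal 5% test at n = 33 is:

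| Common incidence | Chi-squared | Exact trend |
|---|---|---|
| 2% | 2.0% | 1.6% |
| 5% | 3.4% | 3.3% |
| 10% | 4.3% | 3.8% |

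Both tests err on the conservative side, and the trend test at least as much.

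**Cost of two tests.** With no effect at all, the chance that at least one of the two is significant is about 5% to 7% for a common incidence of 5% to 15% at 28 or 33 per arm.

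**The case against.** An overall chi-squared is a valid and conventional test for safety outcomes on which the trial was not sized, and nothing in the analysis section is wrong in itself. The remarks on dose-dependence are background statements about the drug class. The stated aims speak of safety at varying doses and of the incidence of adverse events, not of a trend hypothesis, and the rationale names sedation, dizziness and oedema but not headache or visual disturbance. All power figures rest on assumed rates. A fallback for small expected counts is a detail that a statistical analysis plan would normally carry.

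Most of this stands. It makes the point an improvement in efficiency rather than the correction of an error, and the lack of a small-count rule is not counted against the protocol. It does not remove the point, because the protocol fixes one test that ignores order and says that nothing further is planned.

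Three stronger readings are tempting and not supported. First, a reader might infer that sparse tables make the chi-squared test misleading and that an exact trend test repairs this. Sparseness depends on rates that the protocol does not give, the error is conservative, and the exact trend test shares it. Second, a reader might infer that a trend test would find a gradient far more often. The ratio is about 1.3 to 1.5 in the cases above, and at 5/10/15/20% the gradient is still missed more often than found; the arm size is the main limit. Third, a reader might infer that the trend test should replace the overall test. The plateau and umbrella rows show why it should not.

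**Conclusion.** The point holds as a cheap improvement. The planned side-effect comparison is valid, but it ignores dose order in a trial that studies safety across equally spaced doses and describes the side effects as dose-dependent. Under steady gradients, a trend test on the same data has about 12 to 17 points more power.

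This rests on assumed incidences, on a roughly steady rise over 0 to 75 mg, and on 28 to 33 analysed per arm. The analysis section elsewhere expects 20% withdrawal, which would leave about 26 per arm (33 × 0.8 = 26.4); at 26 and 5/10/15/20% the powers are 0.23 and 0.35. If the dose-response has another shape, the advantage shrinks or reverses.

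A trend test cannot recover events that never reach the table. The protocol withdraws participants with severe side effects and analyses only those who complete 72 h. That is a separate matter, and this change does not touch it.

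**What to change.** In the analysis section, for each side effect (any occurrence within 72 h):

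- add a prespecified exact Cochran-Armitage trend test over 0, 25, 50 and 75 mg;
- keep the overall between-group comparison beside it, in its exact (Fisher-Freeman-Halton) form when expected counts are below 5;
- report each arm's incidence and each dose-minus-placebo risk difference with a 95% interval;
- state that the trend test is read for a dose gradient and the overall test for any other pattern, and that a non-significant overall test is not evidence of no dose effect.

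The section on additional analyses needs no change if the trend test is listed with the main methods. The cost is a few sentences, with no new data or participants. The price is two tests per side effect, with the 5% to 7% chance of a false signal shown above, which is why the role of each must be stated beforehand.

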**Methods:**

This is a prospective, randomized controlled, double-blind study. A total of 132 participants will be randomly assigned to the placebo (*n* = 33) group or to the pregabalin 25 mg (*n* = 33), 50 mg (*n* = 33), or 75 mg (*n* = 33) groups. Each participant will be administered placebo or pregabalin once prior to surgery and every 12 h after surgery for 72 h. The primary outcome will be the visual analogue scale pain score, total dose of administered intravenous patient-controlled analgesia, and frequency of rescue analgesic administered for 72 h from arrival to the general ward after surgery, subdivided into four periods: 1–6 h, 6–24 h, 24–48 h, and 48–72 h. The secondary outcomes will be the incidence and frequency of nausea and vomiting due to intravenous patient-controlled analgesia. Safety will be assessed by monitoring the occurrence of side effects such as sedation, dizziness, headache, visual disturbance, and swelling.

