### Criteria for discontinuing or modifying allocated interventions

Participants who present with severe drowsiness, dizziness, visual disturbance, or swelling that precludes the use of pregabalin will discontinue the trial and stop taking their allocated treatment. Participants who develop infection, nerve injury, hematoma, or metal-related complications following surgery or those who request discontinuation will also be excluded from the trial.

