### Methods for additional analyses (e.g. subgroup analyses)

No additional analyses are planned.

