### Adverse event reporting and harms

During the intervention, the principal investigator will actively seek and be informed of any occurring adverse events. All adverse events will be recorded in the CRF. The principal investigator will report any serious adverse events to the institutional review board within 15 days of notice. Adverse events that are not serious will be reported every 3 months. When reporting adverse events or harm, the causality, timing of occurrence, severity, seriousness, and provided management will be reported together.

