The adverse effects of postoperative pregabalin have not been investigated in detail. Most studies focused on the efficacy and side effects of pregabalin when used preoperatively [25, 27]. Kim et al. [18] reported the incidence of pregabalin side effects until 48 h postoperatively, but the doses of pregabalin used in that study were 75 mg and 150 mg. Our study will focus on the efficacy and adverse effects of postoperative pregabalin at lower doses (25 mg, 50 mg, and 75 mg).

In conclusion, our study will provide evidence on the efficacy of pregabalin for postoperative pain relief after spinal surgery without major side effects even when used at the low dose of 25 mg.

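### Side effects are compared between arms only by incidence, without dose order and in completers, which cannot support a conclusion about major side effects

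*Protocol article*

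**What the plan says.** The protocol article, under Statistical methods for primary and secondary outcomes, states the safety aim as incidence ("the study aims to assess the incidence of adverse events during this period") and fixes the method: "the incidence of side effects (sedation, dizziness, headache, visual disturbance, and swelling), will be compared between the groups using the chi-squared test". The abstract is in line with this: "Safety will be assessed by monitoring the occurrence of side effects". Methods for additional analyses adds "No additional analyses are planned". The section on non-adherence and missing data limits the analysis to eligible patients who complete the 72 h without dropout. It also has the exact reason for each withdrawal documented.

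Severity enters in three other places. Under Adverse event reporting and harms, "the causality, timing of occurrence, severity, seriousness, and provided management will be reported together". The rule on leaving the trial reads "Participants who present with severe drowsiness, dizziness, visual disturbance, or swelling that precludes the use of pregabalin will discontinue the trial" (section Criteria for discontinuing or modifying allocated interventions). The last sentence of the Discussion expects evidence of pain relief "without major side effects even when used at the low dose of 25 mg". The article does not define what a major side effect is.

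**The concern.** Safety by dose is half of the stated objective, and the Background gives dose-dependent sedation, dizziness and peripheral oedema as the reason for studying several doses. The article treats severity as what counts: it decides who leaves the trial, and it is the subject of the closing conclusion. The planned comparison uses none of it. Mild drowsiness and severe drowsiness count alike, and the chi-squared test treats the four doses as unordered labels. Some of the severe cases are not even in the table, because they have left the completer set.

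Every arm also receives a background fentanyl infusion (Relevant concomitant care), so any-grade sedation or dizziness may be common under placebo too. An any-versus-none comparison then has little room to separate the doses. The risk is that the plan is followed exactly, the four arms show similar incidence, and this is read as absence of major side effects.

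**Working it through.** **Inputs from the article.** Four arms at 1:1:1:1, 28 per arm before loss and 33 randomised, two-sided 5% level. The arm size reproduces: a four-group one-way ANOVA with f = 0.448, alpha 0.0167 and power 0.95 needs 28 per group (power 0.955 at 112 in total), and 28/0.85 = 32.9, so 33. The article gives no side-effect rates and no severity distribution. All rates below are assumptions.

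**Step 1: pure severity shift, nobody removed.** If incidence is the same in every arm, the any-versus-none table has the same distribution in every arm, so the planned test can reject only at its error rate. Simulation (4000 runs per scenario, 28 or 33 per arm) used incidence of 30–50% in all arms. The severe share of events was 10% in three arms and 50–80% in the top arm, or rose 10/20/35/60%. Rejection rates:

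- any versus none, chi-squared: about 4.5–5.5%
- severe versus not severe, chi-squared: about 32–98%
- Kruskal–Wallis on none/mild/severe: about 5–27%

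**Step 2: the same shift when severe cases leave the analysis set.** Let i be true incidence and s the severe share of events. If all severe cases are removed (the extreme case), the expected incidence among completers is i(1 − s)/(1 − is). With i = 0.40:

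- s = 0.10: 0.36/0.96 = 37.5%
- s = 0.50: 0.20/0.80 = 25.0%
- s = 0.80: 0.08/0.68 = 11.8%

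The arm with more severe events shows the lower incidence. Over the Step 1 scenarios the completer test rejects in about 10–56% of runs, and the difference it detects points in favour of the worse dose.

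**Step 3: dose moves both incidence and grade.** 28 per arm, cumulative odds ratio 3.5 at 75 mg, log-linear in dose. The last row is instead a pure shift: 70% any-grade in all arms, with the moderate-or-severe share of those affected rising from 10% to 50%. Approximate power:

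| Placebo none/mild/moderate/severe | Any-grade chi-squared | Kruskal–Wallis on worst grade | Dose-ordered rank test on grade | Dose trend on yes/no | Moderate-or-severe chi-squared |
|---|---|---|---|---|---|
| 30/40/20/10% | 31% | 58% | 76% | 49% | 50% |
| 20/40/30/10% | 20% | 58% | 74% | – | – |
| 20% any-grade (rare) | 45% | 46% | 65% | 63% | – |
| Pure shift at 70% any-grade | 5% | 21% | 33% | – | 62–64% |

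A dash means that no figure is used here. Repeat simulations differ by two or three percentage points.

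**Reading.** In the first row, dose order alone takes power from 31% to 49%, and grade takes it on to 76%. With rare events, dose order gives nearly the whole gain (45% to 63%) and grade adds about two points. For a pure severity shift, a moderate-or-severe cut has about twice the power of the dose-ordered rank test. No single test is best throughout.

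**The case against.** Testing incidence is what the article says it will do, in both the abstract and the statistical section, so the comparison does not contradict the stated safety aim. That stands. The mismatch is with the Discussion sentence and with the use of severity elsewhere.

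A reader might infer that a dose which turns mild effects into severe ones would go unseen. The article does not support that. Severe reactions that preclude the drug end participation, the reason for withdrawal is documented, and severity is reported with adverse events. What is missing is any planned comparison of these records between arms. A shift from mild to moderate need not show in withdrawals at all.

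A reader might also take the absence of a severity table as an omission. It is not one: such a table is commonly left to the full protocol or analysis plan, and the statement that nothing further is planned stands under a heading about subgroup-type analyses. The criticism is of the method that the article does fix.

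The power figures rest on favourable assumptions. The first two rows of the table take 70–80% any-grade incidence under placebo, although patients with previous frequent dizziness or headaches are excluded. The fentanyl argument covers sedation and dizziness, not visual disturbance or swelling. Those rows also imply 28% severe at 75 mg (odds 0.10/0.90 × 3.5 = 0.389; 0.389/1.389 = 28%) with everyone analysed, while the article expects losses of 15% or 20%. This stands as a limit on the size of the gain. It also shows that regrading completers alone would not be enough.

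**Conclusion.** The concern holds in a limited form. The one between-arm safety comparison that the article fixes is incidence without grade or dose order, in completers, and it cannot support a statement about major side effects. With all patients kept, it has no power beyond about 5% against a pure severity shift, whatever the common incidence. With severe cases removed, it can reverse the apparent direction. How far it reverses depends on how many severe reactions lead to leaving the trial, which the documents do not let us estimate.

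The gain from a better analysis depends on assumed rates. It is large when any-grade effects are common and comes almost entirely from dose ordering when they are rare. A reader might infer that an ordinal rank test alone is the cure. It is not: it would miss the pure severity shift examined here about two times in three. The change is cheap and worth making, but it does not show that harm would be hidden from the investigators.

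**What to change.** In Statistical methods for primary and secondary outcomes:

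1. Define a major side effect on one agreed grading scale (none, mild, moderate, severe), fixed before unblinding.
2. For each of the five side effects, compare by arm the number of patients with a moderate-or-severe (or severe) worst grade over 72 h, or who stopped for that side effect. Use all randomised patients who took a dose, and give exact confidence intervals. The event that led to stopping has already been observed, so this needs no further follow-up.
3. Add a test that respects dose order: a trend test on incidence, or an ordinal model with dose on worst grade.
4. Keep any-grade incidence as description.

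Limit the closing sentence of the Discussion to what these comparisons can support.

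The cost is analysis wording, one agreed severity scale and a severity tick-box beside the five side-effect rows of Table 2 on the case report form. No extra patients or visits are needed, and no treatment rule changes. Severity is already reported with adverse events, but the scale must be applied in the same way in all arms.
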